**Primary outcome**							
Pain self-efficacy	FESS [25]	Continuous	10 to 60	x	x	x	x
**Secondary outcomes**							
* Health and health-related outcomes*							
Current health status	COPSOQ-Item [30]	Continuous	0 to 10	x	x	x	x
Mental health	IRES-24 [31]	Continuous	0 to 10	x	x	x	x
Functional capacity	IRES-24 [31]	Continuous	0 to 10	x	x	x	x
Pain	IRES-24 [31]	Continuous	0 to 10	x	x	x	x
Action-oriented coping	FESV [32]	Continuous	4 to 20	x	x	x	x
Cognitive restructuring	FESV [32]	Continuous	4 to 20	x	x	x	x
Subjective coping competence	FESV [32]	Continuous	4 to 20	x	x	x	x
Mental distraction	FESV [32]	Continuous	4 to 20	x	x	x	x
Counter activities	FESV [32]	Continuous	4 to 20	x	x	x	x
Relaxation	FESV [32]	Continuous	4 to 20	x	x	x	x
Motivational self-efficacy	3 Items, based on [33]	Continuous	3 to 12	x	x		
Disorder and treatment knowledge	Own development	Continuous	0 to 50	x	x	x	x
Self-efficacy in practicing gained knowledge	Own development	Continuous	0 to 20	x	x	x	x
Electronic health literacy	eHEALS [34]	Continuous	8 to 40	x	x	x	x
Self-informing behaviour	Own development	Ordinal	1 to 6	x		x	x
Adherence to exercises	Own development	Ordinal	1 to 5			x	x
Adherence to knowledge	Own development	Ordinal	1 to 5			x	x
*Work functioning outcomes*							
Work ability in relation to work demands	Work Ability Index [35, 36]	Continuous	2 to 10	x	x	x	x
Self-rated work ability	Work Ability Index [37, 38]	Continuous	0 to 10	x	x	x	x
Current sickness absence	Own development	Binary		x	x	x	x
Sickness absence in weeks	Own development	Continuous	1 to 13 or 26	x		x	x
Employment	Own development	Binary		x		x	x
Employment contract	Own development	Nominal		x			
Shift working	Own development	Nominal		x			
*Patient satisfaction*							
Patient satisfaction	ZUF-8 [39]	Continuous	8 to 32		x		
System usability (intervention group only)	SUS [40]	Continuous	0 to 100		x		
Overall assessment of the Caspar application (intervention group only)	Based on Thielsch [41]	Ordinal	1 to 5		x		
Frequency of Caspar use (intervention group only)	Own development	Ordinal	1 to 6		x		
Type of electronic device (intervention group only)	Own development	Nominal			x		
*Rehabilitation aftercare*							
Physical activity	Own development	Nominal				x	x
Aftercare programs	Own development	Nominal				x	x
Reasons for non-use of aftercare	Own development	Nominal				x	x
**Other outcomes**							
Sociodemographic information	Own development	Various (year of birth, gender etc.)		x			
Treatments during the rehabilitation program	Standardized discharge report [42], according to the classification of therapeutic services [43]	Continuous (minutes or hours)			x		

### Primary outcome

The primary outcome is pain self-efficacy, which is measured by the German adaption of the Pain Self-Efficacy Questionnaire (PSEQ, German: Fragebogen zur Erfassung der schmerzspezifischen Selbstwirksamkeit, FESS) [25, 44]. The questionnaire consists of ten statements, which ask to what extent persons are convinced that they can carry out certain activities despite the pain. Accordingly, participants rate each statement on a scale from 1 to 6 (1 = completely convinced, 6 = not convinced at all). All scores are added up to an overall score (range from 10 to 60). Higher scores indicate better pain self-efficacy. Good validity of the FESS was shown in a rehabilitation setting [25].

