To assess how well the patients adhered to the knowledge learned from the back school after rehabilitation ended, we ask them the self-constrcuted question: How often did you apply the knowledge you learned from the back rehabilitation to everyday life after the end of the rehabilitation? Five potential answers are provided (1 = several times a week, 2 = once per week, 3 = several times per month, 4 = rare, 5 = never).

*Work functioning outcomes:* Work ability is measured by three questions of the work ability index [35, 36]. The first and second question ask for the current ability to do physical work and mental work. For either question, five choices to answer are provided (5 = very good, 4 = rather good, 3 = moderate, 2 = rather bad, 1 = very bad). The score of the first two questions is added up to an overall score, which ranges from 2 to 10. A higher score is related to better work ability. Scoring is weighted by the type of work (mental, physical, or both mental and physical). A third question asks participants to rate their work ability from 0 to 10 points (0 = completely unable to work, 10 = best work ability) [37, 38].

Sickness absence is measured by self- developed questions, which assess if people are currently on sick leave and how many weeks patients were on sick leave during the last 6 months (baseline and 12-month follow-up) or 3 months (3-month follow-up).

Employment is assessed by a self- developed item, which allows a distinction between employed and non-employed persons. Additionally, we ask for the employment contract (e.g., permanent) and shift work.

*Patient satisfaction:* Patient satisfaction is assessed by the German version of the Client Satisfaction Questionnaire (CSQ, German: Fragebogen zur Messung der Patientenzufriedenheit, ZUF-8) [39, 45], which contains eight questions and four options to answer every question. After reversing four of the items, a total score is calculated ranging from 8 to 32 points. A higher score represents higher satisfaction.

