### Statistical analysis

We analyze the short-term effects (end of rehabilitation and 3-months follow-up) and long-term effects (12-months follow-up) to show non-inferiority of the hybrid rehabilitation program. The results of the short- and long-term effects will be published separately.

To test the primary hypothesis of non-inferiority, the confidence interval method is applied [47, 48]. We determined -4 points as the non-inferiority margin. Four points are slightly below the smallest clinically important difference (5.5 to 8.5 points) reported in a recent systematic review on pain self-efficacy in patients with low back pain [49]. We assume non-inferiority of the hybrid rehabilitation if the lower boundary of the one-sided 95% confidence interval (CI) exceeds -4 points.

The estimate of the treatment effect is adjusted for the baseline scores of the dependent variable, as well as for the treatment center (outpatient rehabilitation center). To estimate group differences for continuous and binary outcome variables, linear or logistic regression is calculated. Regression coefficients or odds ratios and their 95% CI are determined. Confidence intervals are two-sided for all secondary outcomes.

Age, sex, level of education, electronic health literacy, and motivational self-efficacy are considered as moderators of the treatment effect on our primary outcome variable. The interaction effects are assessed through p-values. All secondary outcome variables are tested on superiority of the intervention group, and we present p-values. We test superiority to identify potential group differences that, in the case of non-inferiority, can be used to formulate a preference for one of the two treatments [50].

In order to perform an intention-to-treat analysis, missing values are imputed by multiple imputation using 20 independent data sets [51, 52]. The parameter estimates are combined according to Rubin’s rules [53].

A sensitivity analysis also calculates unadjusted estimates for the intention-to-treat analysis. An additional sensitivity analysis is conducted as complete case analysis. Like in the primary analysis, we adjust for the baseline scores of the dependent variable and for the treatment center. We also conduct a per-protocol analysis, including only individuals in both groups who participated in six of the seven back school modules.

Withdrawal from consent leads to deletion of the participant’s data.

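### The printed item coding of the primary outcome runs against its stated direction, and the non-inferiority rule is valid only if higher scores are better

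*Protocol article*

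**What the plan says.** The Primary outcome section of the protocol article makes three statements about the FESS, one after another:

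- Item coding: "Accordingly, participants rate each statement on a scale from 1 to 6 (1 = completely convinced, 6 = not convinced at all".
- Scoring: "All scores are added up to an overall score (range from 10 to 60".
- Direction: "Higher scores indicate better pain self-efficacy".

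Table 3 lists the instrument with the same 10 to 60 range and gives neither a direction nor a recode.

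The Statistical analysis section sets the margin, "We determined -4 points as the non-inferiority margin", and the decision rule: "We assume non-inferiority of the hybrid rehabilitation if the lower boundary of the one-sided 95% confidence interval (CI) exceeds -4 points". It does not say which arm is subtracted from which.

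For another instrument, the ZUF-8, the Secondary outcomes section does spell out a recode: "After reversing four of the items, a total score is calculated ranging from 8 to 32 points". It also states that the negatively worded SUS items are reversed.

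**The concern.** With the printed anchors and a plain sum, a patient fully convinced on all ten items scores 10, the minimum. A patient not convinced on any item scores 60, the maximum. The stated direction says the opposite, so the three statements cannot all be true.

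This is the primary endpoint, and the direction decides which tail of the confidence interval protects patients. Testing a lower bound against a negative margin is right when a worse hybrid programme produces a negative difference. On a score where higher is worse, a loss of self-efficacy in the hybrid arm appears as a positive difference and moves the lower bound away from -4. The rule would then pass a harmful programme and fail a beneficial one. The signs of the planned moderator effects on this outcome would be reversed as well.

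**Working it through.** **1. Direction of the sum as printed.** Ten items at 1 (fully convinced) give 10 × 1 = 10. Ten items at 6 (not convinced) give 10 × 6 = 60. Recoding each item as 7 minus the response gives a total of 70 minus the sum, so these become 60 and 10. The range is 10 to 60 either way, so the range in Table 3 cannot tell the two apart.

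**2. Comparison with the other scores.** The other simply summed scales with printed anchors are the FESV subscores, motivational self-efficacy, knowledge, self-efficacy in practicing knowledge, eHEALS and the two-item work ability score. All have anchors that agree with higher being better. Among these, the FESS is the only one whose anchors run the other way.

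**3. Inputs for the size of the effect.** From Sample size: one-sided error 5%, power 90%, required total 242 (121 per arm), planned total 320 (160 per arm). From Statistical analysis: margin -4, and a cited clinically important difference of 5.5 to 8.5 points. The article takes its SD from an earlier trial but does not print it, so 242 cannot be reproduced independently. The SD that 242 implies, with a true difference of zero, is

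SD = 4 × √(121/2) / (1.645 + 1.282) ≈ 10.63.

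Put back into the usual formula for comparing two means, 10.63 returns 242. It is an assumption, and I also used 9 and 12.

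**4. Probability of declaring non-inferiority.** Let d be the true benefit of the hybrid arm in self-efficacy points (negative means worse). Take the difference as hybrid minus conventional, which the negative margin implies. Then

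P = Φ((s·d + 4)/SE − 1.645), with SE = SD × √(2/n),

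where s = +1 if higher is better and s = −1 if the items are summed as printed. With SD 10.63 and n = 160, SE = 10.63 × √(2/160) ≈ 1.19.

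| True effect of hybrid, d | Higher is better | Summed as printed |
|---|---|---|
| −8.5 | about 0 | about 1.00 |
| −5.5 | 0.002 | about 1.00 |
| −4 | 0.050 | about 1.00 |
| −2 | 0.515 | 0.9997 |
| 0 | 0.957 | 0.957 |
| +2 | 0.9997 | 0.515 |
| +4 | about 1.00 | 0.050 |
| +5.5 | about 1.00 | 0.002 |

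Example at d = −4: oriented correctly, (−4 + 4)/1.19 − 1.645 = −1.645, so P = 0.05. As printed, (4 + 4)/1.19 − 1.645 ≈ 5.1, so P ≈ 1.00.

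**5. Sensitivity.** For SDs of 9 to 12, with 121 or 160 per arm, the as-printed probability at a true 4-point deficit is never below 0.9998. With 121 per arm and SD 10.63, the probability at no true difference is 0.90 under either orientation, which is the planned power. The required 242 does not depend on the orientation.

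**The case against.** The strongest reply is that this may be only a reporting slip. The stated direction, the negative margin and the lower-bound rule agree with one another; only the anchors, or an unstated recode, are out of line. Someone who takes the stated direction seriously would recode or use correctly anchored items, and nothing shown proves that the data will be analysed the wrong way round.

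The article also leaves out scoring steps elsewhere. The SUS as described gives 25 to 125 (ten items coded 1 to 5, summed, times 2.5), yet a range of 0 to 100 is stated. The IRES-24 conversion to 0 to 10 has no formula. The reversals stated for the ZUF-8 and SUS concern only some items of each scale, so silence about a whole-scale recode of the FESS is weak evidence. Finally, the probabilities in the table follow mechanically from a change of sign; they do not say how likely the error is.

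Most of this stands, and it limits the finding: the wrong-tail result is conditional on summing as printed and leaving the rule alone. It does not remove the contradiction. The Data management section says the entry forms carry the questionnaire's own questions and values. If the printed anchors are accurate, raw data therefore enter in the wrong direction, and only an undocumented step would correct them. Nor is this a detail that can be left to an analysis plan, because the article prints the coding, the scoring and the direction, and they conflict.

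**Conclusion.** The concern holds. The item coding, the plain sum and the stated direction of the primary outcome are incompatible, and nothing else in the article reconciles them. The only non-inferiority rule is valid under just one of the two possible directions.

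If the score is built as printed and the rule is unchanged, the error rate at the margin rises from 0.05 to about 1.00. A programme 5.5 points worse, the lower end of the range the article cites as clinically important, would pass with probability about 1.00 instead of 0.002. With no true difference the two orientations pass equally often (0.957), so a passing result would not reveal the error.

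The probabilities rest on a back-solved SD of about 10.6, a normal approximation without baseline adjustment, full data on 320 patients, and the difference taken as hybrid minus conventional. The conclusion is insensitive to SDs from 9 to 12. Whether the fault is a misprint or a missing recode cannot be determined from the article. Because it concerns the primary endpoint in an unblinded trial, it should be settled in writing before outcomes are compared by arm.

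**What to change.** Compare the printed questionnaire with the data-entry form and the scoring code, then make one of two corrections:

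- If the questionnaire runs from 1 = not convinced to 6 = fully convinced, correct the anchors in the protocol.
- If it runs as the article prints it, add that each item is recoded as 7 minus the response before summing (total = 70 minus the raw sum).

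In either case, state beside the -4 margin that the difference is hybrid minus conventional on a score where higher is better.

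An optional safeguard is to check, on baseline data pooled over arms, that the FESS correlates positively with the IRES-24 pain and functional capacity scores, on which higher is also better.

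The cost is one or two sentences and a check of the scoring code. The sample size stays the same, and no patients or new data are needed. The check should be done while the paper questionnaires still exist, since the Confidentiality section has them destroyed when the study is complete.

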### Secondary outcomes

*Health and health-related outcomes:* The current health status is assessed through one item of the COPSOQ (Copenhagen Psychosocial Questionnaire) [30]. The participants rate their current health condition on a scale from 0 to 10 (0 = worst imaginable state of health, 10 = best imaginable state of health).

Mental health, functional capacity, and pain are assessed with the IRES-24 questionnaire, which was developed as a comprehensive generic tool to measure outcomes of rehabilitation in Germany [31]. For mental health and functional capacity, eight questions or statements each are considered. Participants have five options to answer each question or statement (1 = usually, 2 = quite often, 3 = sometimes, 4 = rare, 5 = never). Pain is assessed using three questions with six options to answer (1 to 6 points). The mean scores of mental health, functional capacity, and pain are converted into a scale ranging from 0 to 10. Higher scores indicate better mental health or functional capacity and less pain.

Cognitive and behavioral pain management are determined by six subscores of the FESV questionnaire (Fragebogen zur Erfassung der Schmerzverarbeitung) [32]: action-oriented coping, cognitive restructuring, subjective coping competence, mental distraction, counter activities, relaxation. Each score is based on four statements. Participants rate each statement on a scale from 1 to 6 (1 = not true at all, 6 = absolutely true). The score of each statement is added up to an overall subscore ranging from 4 to 24, respectively. A higher overall score indicates a better outcome. The validity of the questionnaire was shown for a broad spectrum of pain patients [32].

Motivational self-efficacy is determined by ratings of three statements based on Schwarzer et al. [33]. Participants have four options to rate three statements (1 = it is not true, 2 = hardly true, 3 = rather true, 4 = true). The score of each question is added up to an overall score, which ranges from 3 to 12 points. A higher score shows better motivational self-efficacy.

Participants are expected to accumulate disorder and treatment knowledge on back pain during the rehabilitation. This knowledge is rated by ten self-developed questions (e.g., How well informed do you feel about the difference between specific and non-specific back pain?) A 6-point scale is provided for every question (0 = not informed at all, 5 = very good informed). The questions refer to all modules of the back school. The scores of the ten questions are added up to an overall score, which ranges from 0 to 50 points. A higher score indicates more disorder and treatment knowledge.

Participants are expected to improve their self-efficacy in practicing gained knowledge. Self-efficacy in practicing gained knowledge is tested by four self-developed questions (e.g., How confident do you feel in doing exercises to strengthen your back muscles?) A 6-point scale is provided for every question (0 = not confident at all, 5 = very confident). The questions are based on modules three and six of the back school. The scores of the four questions are added up to an overall score, which ranges from 0 to 20 points. A higher score indicates more self-efficacy in practicing gained knowledge.

Electronic health literacy is measured by the eHEALS (E Health Literacy Scale) [34]. Eight questions ask the participants how they rate their skills to obtain health-related information from the internet. Five choices to answer are provided for every question (1 = disagree, 2 = rather disagree, 3 = neutral, 4 = rather agree, 5 = totally agree). The score of each question is added up to an overall score. The overall score ranges from 8 to 40 points. A higher score is related to higher electronic health literacy.

Self-informing behavior is assessed using a self-developed question, which asks how frequently the participant informed themself about back pain or chronic pain in the past 3 months. Six potential answers are provided (1 = daily, 2 = several times per week, 3 = once per week, 4 = several times per month, 5 = rarely, 6 = never).

To assess how well the patients adhered to the exercises from the back school after the rehabilitation ended, we ask them the self- developed question: How often did you do the exercises from the back rehabilitation after the end of the rehabilitation? Five potential answers are provided (1 = several times a week, 2 = once per week, 3 = several times per month, 4 = rare, 5 = never).

To assess how well the patients adhered to the knowledge learned from the back school after rehabilitation ended, we ask them the self-constrcuted question: How often did you apply the knowledge you learned from the back rehabilitation to everyday life after the end of the rehabilitation? Five potential answers are provided (1 = several times a week, 2 = once per week, 3 = several times per month, 4 = rare, 5 = never).

*Work functioning outcomes:* Work ability is measured by three questions of the work ability index [35, 36]. The first and second question ask for the current ability to do physical work and mental work. For either question, five choices to answer are provided (5 = very good, 4 = rather good, 3 = moderate, 2 = rather bad, 1 = very bad). The score of the first two questions is added up to an overall score, which ranges from 2 to 10. A higher score is related to better work ability. Scoring is weighted by the type of work (mental, physical, or both mental and physical). A third question asks participants to rate their work ability from 0 to 10 points (0 = completely unable to work, 10 = best work ability) [37, 38].

Sickness absence is measured by self- developed questions, which assess if people are currently on sick leave and how many weeks patients were on sick leave during the last 6 months (baseline and 12-month follow-up) or 3 months (3-month follow-up).

Employment is assessed by a self- developed item, which allows a distinction between employed and non-employed persons. Additionally, we ask for the employment contract (e.g., permanent) and shift work.

*Patient satisfaction:* Patient satisfaction is assessed by the German version of the Client Satisfaction Questionnaire (CSQ, German: Fragebogen zur Messung der Patientenzufriedenheit, ZUF-8) [39, 45], which contains eight questions and four options to answer every question. After reversing four of the items, a total score is calculated ranging from 8 to 32 points. A higher score represents higher satisfaction.

*Use of the digital intervention:* The digital intervention is rated by the intervention group only. The system usability of the Caspar application is determined using the System Usability Scale (SUS) [40]. Participants rate ten statements on the utilization of the Caspar application by a 5-point scale (1 = strongly disagree, 5 = strongly agree). Negatively formulated questions are reversed before calculation. The sum of all 10 questions is calculated and multiplied by 2.5. The maximum value is 100, minimum value is 0.

An overall assessment of the Caspar application is assessed by grades from 1 to 5 (1 = very good, 2 = good, 3 = satisfying, 4 = sufficient, 5 = insufficient) [41].

The way of using the Caspar application is clarified by two self- developed questions. The first question asks how frequently participants make use of the Caspar application during the last 3 weeks. Six potential answers are provided (1 = daily, 2 = several times per week, 3 = once per week, 4 = several times per month, 5 = rarely, 6 = never). An additional question asks what electronic device was used. Multiple responses are possible (1 = laptop, 2 = computer, 3 = mobile phone, 4 = TV, 5 = tablet, 6 = other).

*Rehabilitation aftercare:* Three self- developed questions on rehabilitation aftercare assess which physical activity options were used in the last 3 months (including digital applications) (1 = rehabilitation sport, 2 = functional training, 3 = sports club, 4 = gym, strength endurance training or medical training therapy, 5 = endurance sports, e.g., running, Nordic walking, 6 = Yoga, Pilates, Qi Gong, or Tai Chi, 7 = I have not exercised in the last 3 months, 8 = other), which services were used in the last 3 months? (1 = none, 2 = T-RENA [exercise therapy rehabilitation aftercare], 3 = Caspar Health, 4 = social/vocational counseling, 5 = Psy-RENA [psychosomatic rehabilitation aftercare], 6 = occupational therapy, 7 = gym-based physiotherapy, 8 = IRENA [intensified rehabilitation aftercare], 9 = psychological counseling, 10 = functional training, 11 = physiotherapy, 12 = rehabilitation sport, 13 = other), and reasons for not participating in an aftercare program (1 = not provided by the outpatient rehabilitation center, 2 = no need, 3 = none of the rehabilitation aftercare programs around, 4 = no time for rehabilitation aftercare, 5 = no interest in rehabilitation aftercare, 6 = other). For each question multiple responses are possible.

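### The SUS scoring rule as written yields 25 to 125, not the stated 0 to 100; two Table 3 scoring ranges (FESV, sickness absence) also need correction or clarification

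*Protocol article*

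**What the plan says.** **SUS** (Protocol article, Secondary outcomes, paragraph on use of the digital intervention). The item format is: "Participants rate ten statements on the utilization of the Caspar application by a 5-point scale (1 = strongly disagree, 5 = strongly agree"). Then: "Negatively formulated questions are reversed before calculation". The total is defined by: "The sum of all 10 questions is calculated and multiplied by 2.5. The maximum value is 100, minimum value is 0". Table 3 repeats 0 to 100, with one assessment at the end of rehabilitation, in the intervention group only.

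**FESV** (same section, cognitive and behavioral pain management). "Each score is based on four statements", and "Participants rate each statement on a scale from 1 to 6 (1 = not true at all, 6 = absolutely true"). The text continues: "The score of each statement is added up to an overall subscore ranging from 4 to 24, respectively". Table 3 lists 4 to 20 for each of the six subscales.

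**Sickness absence** (same section, work functioning outcomes). The question is "how many weeks patients were on sick leave during the last 6 months (baseline and 12-month follow-up) or 3 months (3-month follow-up"). The text gives no numerical range. Table 3 gives 1 to 13 or 26 weeks and labels the outcome continuous.

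**The concern.** The SUS paragraph gives both an algorithm and a result, and the two disagree. Anyone who programs the total from the sentence gets scores that cannot be read against the 0 to 100 scale that the protocol says it uses. The error is not always visible: a wrong score stays inside the printed limits unless the correct score is above 75.

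For the FESV, the text and Table 3 give different maxima for six outcomes that are measured at all four time points and, under Statistical analysis, tested for superiority with p-values. The values missing from the table are the top four. Higher is better on these scales, so they are the best outcomes.

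For sickness absence, a scale that starts at 1 leaves open what is recorded for a patient with no sick leave.

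**Working it through.** **Method.** For a summed scale, range = (items × item minimum × multiplier) to (items × item maximum × multiplier).

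**Control: scales whose stated range is reproduced.**

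| Scale | Items and coding | Computed | Table 3 |
|---|---|---|---|
| FESS (primary) | 10 at 1–6 | 10–60 | 10–60 |
| Motivational self-efficacy | 3 at 1–4 | 3–12 | 3–12 |
| Disorder and treatment knowledge | 10 at 0–5 | 0–50 | 0–50 |
| Self-efficacy in practicing knowledge | 4 at 0–5 | 0–20 | 0–20 |
| eHEALS | 8 at 1–5 | 8–40 | 8–40 |
| Work ability | 2 at 1–5 | 2–10 | 2–10 |
| ZUF-8 | 8 with four options, taken as 1–4 | 8–32 | 8–32 |

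The method therefore matches how the protocol derives its ranges.

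**SUS, as written.** Inputs: 10 items, coded 1 to 5, multiplier 2.5. Reversing a 1–5 item as 6 − x leaves it at 1–5.
- Minimum: 10 × 1 × 2.5 = 25.
- Maximum: 10 × 5 × 2.5 = 125.

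The stated 0 to 100 is not reproduced.

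**SUS, other readings.**
- Suppose reversal means 5 − x, applied to k negative items only. Then the minimum is (10 − k) × 2.5 and the maximum is [(10 − k) × 5 + k × 4] × 2.5. For k = 4 this gives 15 to 115, for k = 5 it gives 12.5 to 112.5, and for k = 6 it gives 10 to 110. It would reach 0 to 100 only if all ten items were negative (k = 10).
- A multiplier of 2 gives 20 to 100.
- With every item recoded to 0–4, the sum is 0 to 40, and × 2.5 gives 0 to 100. This is the only reading tried that matches, and the text does not state the recoding.

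The ZUF-8 description in the same section shows how the protocol uses reversal: four of eight items are reversed and the total still runs from 8 to 32. Reversing there does not move the item minimum to 0.

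**Size of the SUS error.** Let S be the sum of ten items at 1–5 after reversal. The intended score is (S − 10) × 2.5 = 2.5S − 25 and the literal score is 2.5S. The difference is exactly 25 for every respondent. An intended 70 becomes 95 and an intended 80 becomes 105. The literal score exceeds 100 only when the intended score exceeds 100 − 25 = 75.

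**FESV.** 4 × 1 = 4 and 4 × 6 = 24, as the text says. A maximum of 20 would need items ending at 5 (4 × 5 = 20). Scores 21 to 24 are 4 of the 21 possible values from 4 to 24.

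**Sickness absence.** Three months is 365.25 / 4 / 7 = 13.04 weeks and six months is 365.25 / 2 / 7 = 26.09 weeks. Both upper limits in Table 3 agree with the recall periods. Only the lower limit of 1 is open.

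**The case against.** **SUS.** The range of 0 to 100 is printed twice, a source for the instrument is cited, and 2.5 combined with 0 to 100 points to 0–4 items. An informed analyst could recover the intended score. The SUS is measured once, in one arm, and enters no group comparison, and a constant shift can be undone from the item data. All of this stands, and it limits the consequence. It does not rescue the sentence, which gives a wrong score when followed. Nor would impossible totals reliably expose the error, since every intended score of 75 or less becomes a plausible number.

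**FESV.** The text is complete and consistent in itself, and nothing says that Table 3 truncates or rejects scores. Data management says that the entry forms carry the questionnaires' own values, so entry limits should not follow the table. This stands: it is a table correction with no demonstrated effect on any estimate.

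**Sickness absence.** A reader might infer that patients without sick leave are dropped, so that the comparison conditions on a post-randomisation outcome. The documents do not support that. The text states no range for Table 3 to contradict, the maxima fit, the exact item wording is not shown, and weeks might be recorded only for those with some absence. Table 3 describes scaling and sets no analysis population. Statistical analysis plans intention to treat with multiple imputation and names no such exclusion. Only a request for clarification remains.

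**Conclusion.** The SUS point holds: the written rule gives 25 to 125, and scores computed from it are 25 points too high. That any reported score will be wrong is conditional on the scoring code following the printed sentence, which the document does not show.

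The FESV point holds as an inconsistency in all six rows of Table 3. On the item format in the text, Table 3 is the side to change.

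For sickness absence, the coding of zero weeks is unclear and no more than that.

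A reader might take the three together as a threat to the trial's conclusions. They are not. All concern secondary outcomes, and the primary outcome range, the −4 point margin and the sample size are unaffected.

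**What to change.** 1. **SUS:** replace the scoring sentence with a rule of this form: positive items are scored as response minus 1 and negative items as 5 minus response; the ten item scores (each 0 to 4) are summed and multiplied by 2.5, giving 0 to 100. Check the scoring code against it.
2. **Table 3, FESV:** change the six rows from 4 to 20 to 4 to 24, in agreement with the text.
3. **Table 3, sickness absence:** state that zero weeks is recorded as 0, so that the range reads 0 to 13 (3-month follow-up) or 0 to 26 (baseline and 12-month follow-up).

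The cost is a few corrected lines and one check of the scoring code. No new data are needed, and no design or primary analysis decision changes.
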